## Abstract

**Background:**

Postprandial distress syndrome (PDS) is the prominent subtype in patients with functional dyspepsia (FD) and currently lacks a satisfactory treatment. Acupuncture has become a promising alternative and complementary therapy for managing FD. However, high-level clinical evidence supporting the use of acupuncture for FD is limited.

**Methods:**

This study is a multicentre, double-dummy, single-blind, randomized, active-controlled trial. Two hundred and one eligible participants will be randomly assigned into three groups: a verum acupuncture plus placebo group, an itopride plus sham acupuncture group, and a sham acupuncture plus placebo group. This study consists of a 1-week screening period, a 4-week treatment period, and a 12-week follow-up period. During the intervention period, participants will receive 12 sessions of verum or sham acupuncture treatment (one session per day, three sessions per week, for 4 weeks) along with 50 mg itopride tablets or 50 mg itopride placebo tablets 3 times a day for 20 days (5 continual days a week for 4 weeks). The response rate (patients who had adequate relief of gastric symptoms will be considered positive responders) and the elimination rate of cardinal symptoms (postprandial fullness and early satiation) are the primary indicators to evaluate the overall acupuncture effect for PDS. Secondary outcome measures will include the Nepean Dyspepsia Symptom Index (NDSI), the short form-Nepean Dyspepsia Life Quality Index (SF-NDLQI), the Hospital Anxiety and Depression Scale (HADS), and related hormone concentrations. Participants’ expectations toward acupuncture treatment will also be assessed, and adverse events will be recorded for safety assessment. All analyses will adhere to an intention-to-treat principle.

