#### Exit/termination criteria

2.3.4

The exit/termination criteria are as follows: (1) patients do not meet the inclusion criteria and are enrolled mistakenly; (2) patients receive other or additional FD treatments during the study period.

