### Sample size calculation

2.11

The sample size for this study was determined based on the responder proportion at the end of a 4-week treatment, with 70.69% for the acupuncture treatment and 55.46% for the itopride treatment, as reported in a previous study (30). The sample size calculation was performed using PASS 15.0 software, with a 1:1 ratio between the verum acupuncture plus placebo group and itopride plus sham acupuncture group. A statistical power of 80% (*β* = 0.2), a one-sided alpha of 0.025 (*α* = 0.025), and a non-inferiority margin of −10% (*Δ* = −10%) were considered in the calculation. The resulting sample size was 57 for each group. Accounting for a 15% dropout rate, each group needed 67 cases, resulting in a total enrollment of 201 cases across three groups.

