### Statistical analysis

2.12

Efficacy analyses will be performed on all patients who were randomized, adhering to the intention-to-treat principle. This approach ensures that all patients are included in the analysis based on the group to which they were initially assigned, regardless of whether they completed the study as intended. Missing data on the primary outcome will be imputed using the multiple imputation method under the missing at-random assumption. If there are significant differences in baseline variables between the two groups, those unbalanced variables will be included as covariates in the analysis of the primary outcome.

We will establish confidence intervals at a 95% level, with a significance level set at 0.05. Continuous data will be reported as mean ± standard deviation (SD) if it is normally distributed. Otherwise, it will be reported as median (interquartile range). For longitudinal continuous data, we will compare groups using repeated-measures analysis of variance (ANOVA), taking into account both group and time-group interactions. Student’s t-test or Wilcoxon rank-sum test will be used for other continuous data. For categorical data, Χ^2^ test or Fisher’s exact test will be applied as appropriate. The strength of linear relationships between variables will be evaluated using linear correlation analysis, and sensitivity analysis will be performed if required. The occurrence of AEs between groups will be summarized using descriptive analysis.

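### The acupuncture-versus-itopride comparison is sized for non-inferiority, but the plan rests on intention-to-treat alone and names no adherence-based analysis beside it

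*Protocol article*

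**What the plan says.** Section 2.11 (Sample size calculation) plans on response rates of "70.69% for the acupuncture treatment and 55.46% for the itopride treatment", with "a one-sided alpha of 0.025" and "a non-inferiority margin of −10" per cent. It arrives at 57 per group, raised to 67 for 15% dropout.

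The Abstract (Methods) says "All analyses will adhere to an intention-to-treat principle". Section 2.12 (Statistical analysis) says "Efficacy analyses will be performed on all patients who were randomized, adhering to the intention-to-treat principle" and keeps patients in their assigned group "regardless of whether they completed the study as intended". Missing primary outcomes are to be multiply imputed under missing at random. The only other analysis mentioned is a sensitivity analysis to be done if required, with no content given.

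Two other sections matter here. Section 2.3.3 counts patients whose symptoms fail to improve and worsen among the dropouts. Section 2.3.4 makes it an exit criterion when "patients receive other or additional FD treatments during the study period", and another when a patient was enrolled by mistake. Neither is tied to an analysis set. Section 2.6.2 collects a medication diary and unused tablets, but no stated analysis uses them.

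**The concern.** In a superiority trial, patients who do not take their treatment make the arms look more alike, so intention-to-treat works against the claim. In a non-inferiority trial, looking alike is the claim. If acupuncture were truly worse than itopride by the margin, and some patients in both arms missed the active component or took other dyspepsia treatment, the intention-to-treat difference would be smaller than the difference among patients treated as planned. Non-inferiority could then be declared partly because of poor adherence. The usual safeguard is a second, adherence-based analysis read alongside intention-to-treat. Here the article states a general rule for the analysis set that suits superiority, and applies it to the one comparison that was sized for non-inferiority.

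**Working it through.** **Inputs.** From section 2.11: pT = 0.7069 (acupuncture), pC = 0.5546 (itopride), margin 0.10, one-sided alpha 0.025 (z = 1.96), power 80% (z = 0.8416), 57 evaluable and 67 enrolled per group.

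**1. Reproduce the sample size.** With unpooled variance,

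n = [pT(1−pT) + pC(1−pC)] × (1.96 + 0.8416)² / (pT − pC + 0.10)²
= 0.4542 × 7.849 / 0.2523² = 56.006, rounded up to 57.

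The Farrington-Manning version gives 56.87, also 57. Dropout: 57/0.85 = 67.06, stated as 67. A two-sided superiority test on the same rates would need 157 per group, so the 57 is a non-inferiority figure.

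**2. Dilution at the margin.** Assume acupuncture is truly worse by exactly 10 points (45.46% v 55.46%), and that a fraction f in each arm responds at a common rate q whatever the assignment. Each arm's rate becomes (1−f)p + fq, so the difference is d = −0.10 × (1−f). The chance of claiming non-inferiority is

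Φ[(d + 0.10)/SE − 1.96], with SE the unpooled standard error at 67 per arm.

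For f = 15% and q = 40%: rates 44.64% and 53.14%, d = −8.5 points, SE = √(0.4961/67) = 0.0861, so Φ(0.015/0.0861 − 1.96) = Φ(−1.786) = 3.7%.

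| f in both arms | ITT difference (points) | False non-inferiority rate |
|---|---|---|
| 0 | −10.0 | 2.5% |
| 10% | −9.0 | 3.3% |
| 15% | −8.5 | 3.7% |
| 25% | −7.5 | 4.8% |

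At f = 15% the rate stays at 3.7% for q anywhere from 20% to 55.46%. Both f and q are assumptions; the protocol gives neither.

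**3. Unequal non-adherence.** Assume an untreated response of 35% and 15% non-adherence in one arm only.
- Verum arm only: 0.85 × 45.46 + 0.15 × 35 = 43.89, difference −11.6 points, which is against the claim.
- Itopride arm only: 0.85 × 55.46 + 0.15 × 35 = 52.39, difference −6.9 points, which is toward it.

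**4. Imputation.** Imputation by arm with dropout at random leaves the difference at −10. Now suppose every dropout is a failure but is imputed at the rate seen in the completers of the same arm.
- 15% dropout in both arms: 45.46/0.85 − 55.46/0.85 = 53.48 − 65.25 = −11.8 points.
- 15% under acupuncture, 5% under itopride: 45.46/0.85 − 55.46/0.95 = 53.48 − 58.38 = −4.9 points.

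**5. At the planned alternative.** If acupuncture is better by 15.2 points, as section 2.11 assumes, 15% dilution in both arms cuts intention-to-treat power at 67 per arm from 86.5% to 78.0%.

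**6. Power of a per-protocol set** at the planned rates, Φ(0.2523/√(0.4542/n) − 1.96): 80.7% at n = 57 and about 75% at n = 50.

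**The case against.** The best defence is that naming intention-to-treat as the analysis set does not forbid a supporting per-protocol set. Section 2.12 limits its wording to efficacy analyses and leaves room for a sensitivity analysis, and a condensed article may leave secondary sets to the analysis plan. This stands in part: a reader might infer that the plan prohibits a per-protocol analysis, and the text does not go that far. However, the Abstract states a rule covering every analysis, and an optional analysis without content cannot act as the check that a non-inferiority claim needs.

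A reader might also infer that imputing dropouts under missing at random in itself favours non-inferiority. The documents do not support this. Section 2.12 does not say that imputation ignores arm, and step 4 shows no effect, an effect against the claim, or an effect toward it, depending on who drops out. It becomes a risk if failure-related dropout, which section 2.3.3 anticipates, is more common under acupuncture.

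Nor should the 3.7% be read as the error rate implied by the protocol's 15%. That figure is a dropout rate, and dropouts are imputed; f is a different quantity. If exit under section 2.3.4 ends data collection, those patients' later outcomes would also be imputed rather than diluted.

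Finally, dilution costs power if acupuncture is truly better. That is correct, but the false-claim rate is judged at the margin, where the direction reverses.

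**Conclusion.** The point holds in a limited form. A comparison sized only for non-inferiority is placed on intention-to-treat alone, with no pre-specified adherence-based counterpart. The effect is modest: the false-claim rate rises from 2.5% to between 3.3% and 4.8% for f between 10% and 25%. This rests on equal dilution in both arms and a true difference exactly at the margin. With unequal non-adherence the bias can go either way, and the protocol gives no figure from which to tell. The plan should be changed on this point, but it does not invalidate the design: the sample size reproduces, and intention-to-treat remains the right primary set for superiority and for comparisons with sham.

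**What to change.** Amend the Abstract and section 2.12 as follows.

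- For verum acupuncture versus itopride on the responder proportion at the end of treatment, pre-specify a per-protocol analysis alongside intention-to-treat. Define the set by confirmed eligibility, a pre-set share of the 12 sessions and of diary-recorded tablets, and no other dyspepsia treatment.
- Report both 95% confidence intervals against the −10% margin, and describe non-inferiority as robust only if the two agree.
- State that multiple imputation is done by arm, and add a sensitivity analysis that does not assume missing at random, since worsening is a listed dropout reason.
- Keep intention-to-treat as the primary set for superiority and sham comparisons.

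The cost is wording and extra analyses, mostly of data already planned for collection. The per-protocol set is not fully protected by randomisation, because membership depends on behaviour after assignment. It also has less power: 80.7% if 57 per arm remain, which assumes that exclusions beyond 67 stay within the 15% allowance, and about 75% if 50 remain. Agreement of both analyses cannot have more power than the weaker one, so the enrolment of 67 per arm should not be presented as certain to support it at 80%.

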**Discussion:**

In conclusion, this trial will determine the efficacy and safety of acupuncture for PDS and provide more high-level evidence to support its application in treating FD.

**Trial registration:**

Identifier [ITMCTR2024000510].

## Introduction

1

Functional dyspepsia (FD) is a common functional gastrointestinal disorder characterized by upper abdominal discomfort or pain without an identifiable organic cause (1). A recent meta-analysis suggests it impacts 8.4% of adults worldwide (2). The Rome IV criteria categorizes FD into three subtypes: epigastric pain syndrome (EPS), postprandial distress syndrome (PDS), and the overlapping form of EPS/PDS (1). PDS, the most common subtype, presents with meal-related symptoms such as postprandial fullness and early satiety. Epidemiological studies from various countries show that PDS accounts for about 60% of FD cases (3, 4) and is more prevalent in Asian populations compared to Western populations (5). Although not life-threatening, the chronic and recurrent nature of FD symptoms significantly impacts patients’ psychological well-being, quality of life (QOL), and social functioning (6). Furthermore, FD imposes a considerable economic burden on patients (7). Therefore, FD has become a significant public health concern requiring heightened clinical attention and research endeavors.

The effective treatment of FD remains an unsolved clinical challenge. FD is recognized as a complex condition with several factors participating in its development (1, 6). Although drugs such as prokinetic agents, acid suppressants, antidepressants, anti-*Helicobacter pylori* medications, and mucosal protectants have been officially recommended for the treatment of FD, single-drug therapy may not address all of the underlying pathophysiological mechanisms of FD, leading to limited efficacy (8). Additionally, these medications may be limited by side effects (9, 10). Therefore, physicians and patients expect more treatments for FD that are both effective and low-risk.

Notably, acupuncture treatment, a method found in traditional Chinese medicine (TCM), can improve FD symptoms through multiple molecular mechanisms (11). It is currently recognized as a significant complementary and alternative therapy for the management of FD (12). Multiple meta-analyses revealed that acupuncture is more effective than the single use of prokinetic drugs or sham acupuncture in improving digestive symptoms and quality of life in patients with FD (13, 14). Moreover, another system review found that acupuncture combined with Western medicine has a synergistic effect in the treatment of FD while helping to reduce the relapse rate within 3–6 months after treatment (15). Additionally, the evidence has shown that acupuncture can regulate gastrointestinal function by improving gastrointestinal motility and reducing visceral sensitivity, which supports the potential of acupuncture as a therapeutic option for FD (16). However, due to limited high-quality evidence (evidence grade B), a recent consensus statement did not endorse acupuncture for FD, highlighting the need for further high-quality RCTs to clarify its therapeutic potential and role in FD management (8).

Previous clinical trials have compared the therapeutic effects of acupuncture with prokinetic agents in patients with FD, revealing acupuncture as a superior way to prokinetic agents (17, 18). However, these studies were open-lable and lacked blinding, potentially allowing patient preferences for acupuncture to influence clinical outcomes. To obtain more high-quality evidence, we design a new randomized trial; this trial will administer different treatments (acupuncture or the drug itopride) in a double-dummy, single-blind design to objectively evaluate the effectiveness and safety of acupuncture for PDS compared to itopride.

## Methods

2

### Study design

2.1

This clinical study is a multicentre, single-blind, double-dummy, randomized, active-controlled trial that compares the efficacy and safety of acupuncture versus itopride in improving upper abdominal discomfort in patients with PDS. The study protocol has been registered with the International Traditional Medicine Clinical Trial Registry (ITMCTR2024000510). It adheres to the Standard Protocol Items: Recommendations for Interventional Trials (SPIRIT) guidelines (Supplementary file 1) (19) as well as the Standards for Reporting Interventions in Controlled Trials of Acupuncture (STRICTA) checklist (Supplementary file 2) (20). The study flowchart is shown in Figure 1.

**Figure 1 fig1:**
[figure not shown]
Flowchart of trial procedures. PR, proportion of responders; ER, elimination rate; NDSI, Neapean Dyspepsia Symptom Index; SF-NDLQI, The Short Form-Nepean Despepsia Life Quality Index; HADS, Hospital Anxiety and Depression Scale.

### Study setting and recruitment

2.2

This clinical trial will be conducted collaboratively by an academic center and three clinical institutions. Researchers from the Hunan University of Chinese Medicine will form an academic center group responsible for experimental design, data analysis and results dissemination. Recruitment, treatment and data collection will occur at the First Affiliated Hospital of Hunan University of Traditional Chinese Medicine, the Second Affiliated Hospital of Hunan University of Traditional Chinese Medicine, and Changsha Hospital of Traditional Chinese Medicine. Recruitment is scheduled to take place at inpatient and outpatient departments in three clinical institutions, and start in December 2024, with the follow-up assessments of all participants completed by December 2027. Recruitment information will be disseminated through various means such as paper flyers, posters, and social platform like Wechat. Participants interested in this trial will be informed about the purpose and process of the study as well as potential risks and benefits. If the patient decides to participate after understanding this information, they will undergo a clinical screening evaluation conducted by registered TCM practitioners with a minimum of 5 years of clinical experience. Eligible patients will sign an informed consent form, receive baseline assessment, and be randomly assigned.

### Eligibility criteria

2.3

#### Inclusion criteria

2.3.1

The study will involve individuals who meet the following criteria: (1) aged 18–60 years and long-term residents of Changsha; (2) diagnosed with FD-PDS according to the Rome IV criteria (21): the individual experiences a sense of fullness and some discomfort in the upper abdomen after normal eating and/or a sense of early satiety which influence the completion of the normal dietary intake occurred several times a week (The past 3 months meet the diagnostic requirements, and symptoms should have been present for a minimum of 6 months prior to diagnosis); (3) no structural abnormalities were detected through upper gastrointestinal endoscopy surveillance; (4) non-refractory FD; (5) patients who are *Helicobacter pylori*-negative or have persistent symptoms after *Helicobacter pylori* eradication for 6 months; (6) Good compliance.

#### Exclusion criteria

2.3.2

The following individuals will be excluded from the study: (1) use drugs, such as prokinetics, acid suppression, mucosal protectants, or other FD-related agents, within 2 weeks; (2) do not tolerate acupuncture; (3) receive acupuncture treatment within 2 weeks; (4) have gastrointestinal diseases other than PDS; (5) pregnant or lactating women and those attempting conception; (6) patients who are participating in other clinical trials; (7) diagnosed with malignancy or other serious conditions, such as severe heart, liver, lung, or kidney dysfunction, severe autoimmune disease, or endocrine diseases; (8) unable to effectively communicate for any reason, such as severe mental illness, cognitive impairment, or impaired language comprehension.

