#### Itopride or placebo

2.6.2

Patients assigned to the itopride plus sham acupuncture group will take 50 mg of itopride orally 3 times a day, 5 days per week, for 4 weeks. Participants in the verum acupuncture plus placebo group and sham acupuncture plus placebo group will receive an itopride placebo that is identical in taste and appearance to actual itopride tablet; they will follow the same frequency and dosage as the itopride plus sham acupuncture group. All patients are instructed to maintain a medication diary to document their usage and return unused medication.

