## Discussion

3

There has been a growing focus in academia on effective treatment for FD in recent years. While some advancements have been achieved in drug treatment for FD (8), the effectiveness is not satisfactory and may come with side effects (9, 10). These problems compel patients to explore other safer and more effective methods in CAM. Acupuncture, a non-pharmacologic therapy in TCM, has been observed to be effective in reliving upper abdominal discomfort and improving QOL in FD patients (13, 14). However, there remains a lack of high-quality clinical studies and evidence supporting the use of acupuncture for FD treatment (8). This study aims to assess the efficacy and safety of acupuncture for FD in a well-controlled trial design, providing evidence to support the clinical application of acupuncture.

For better clinical management, the Rome III Consensus proposed a symptom subtype classification of FD, and Rome IV Consensus adhered to this method (31). Although it remains controversial whether there is any difference in pathogenesis between PDS and EPS (32), choosing a treatment plan based on FD subtypes has become a new trend (33). Evidence shows that PDS is the most prominent subtype, affecting more than 60% of all FD patients (3, 4). Therefore, we selected PDS patients as the subjects of this study and diagnosed FD-PDS patients based on Rome IV criteria. Though multiple mechanisms contribute to PDS development, gastric sensorimotor function disorder has been considered a vital factors (33). Prokinetic agents have been recommended as the first-choice treatment for PDS patients in a Chinese consensus (34). Itopride is a prokinetic agent with a response rate of 55–73% in treating FD and higher drug safety (30, 35, 36). Therefore, we used itopride as a positive drug to evaluate the efficacy of acupuncture in treating PDS, thereby providing more clinical treatment decision-making references.

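### Eligibility excludes patients who do not tolerate acupuncture but not those with known intolerance of, or hypersensitivity to, itopride, the active comparator

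*Protocol article*

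**What the plan says.** Section 2.4 randomises every eligible patient 1:1:1 to verum acupuncture plus placebo tablets, itopride plus sham acupuncture, or sham acupuncture plus placebo tablets. Anyone enrolled may therefore receive either active treatment. In the comparator arm, "Patients assigned to the itopride plus sham acupuncture group will take 50 mg of itopride orally 3 times a day" (section 2.6.2).

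Two entries of the numbered list in section 2.3.2 concern acupuncture: "2) do not tolerate acupuncture; (3) receive acupuncture treatment within 2 weeks". One concerns drugs, and it excludes patients who "use drugs, such as prokinetics, acid suppression, mucosal protectants, or other FD-related agents, within 2 weeks". Exclusion (7) covers malignancy and serious organ, autoimmune or endocrine disease. No entry concerns tolerance of itopride.

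Among the inclusion criteria (section 2.3.1), the one nearest to treatment history is "4) non-refractory FD". The article does not define it.

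Section 2.11 sizes the trial for non-inferiority of acupuncture to itopride, "with a 1:1 ratio between the verum acupuncture plus placebo group and itopride plus sham acupuncture group". Section 2.3.3 treats patients who stop because of intolerable side effects as dropouts. Section 2.12 imputes missing primary outcomes by multiple imputation under missing at random.

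**The concern.** The two active treatments are not screened alike. Patients known to be unsuited to acupuncture are removed before randomisation, while patients known to be unsuited to itopride stay in.

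Two things are at stake. The first is participant protection: a patient with a known reaction to itopride meets the printed criteria once two weeks have passed since the last dose. The second is the fairness of the comparison. In the acupuncture arm such a patient takes placebo tablets and is unaffected; in the itopride arm the same patient may respond less or stop early. The effect falls on the comparator alone, and in a non-inferiority comparison a weaker comparator helps the test treatment. Analysis by intention to treat does not remove this, because the selection happens before randomisation.

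The Discussion makes prior exposure plausible: "Prokinetic agents have been recommended as the first-choice treatment for PDS patients in a Chinese consensus". It does not say how many patients would have reacted to itopride in particular.

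**Working it through.** **1. Side-by-side reading of sections 2.3.1 and 2.3.2**

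| Screening question | Acupuncture | Itopride |
|---|---|---|
| Recent use | Excluded if within 2 weeks | Excluded if within 2 weeks (any dyspepsia-related drug) |
| Known intolerance | Excluded | Not mentioned |
| Earlier non-response | Not named | Not named, though the undefined non-refractory criterion may cover some |

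Only the tolerance row is one-sided against itopride.

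**2. The plan's own figure**

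Inputs from section 2.11: "with 70.69% for the acupuncture treatment and 55.46% for the itopride treatment, as reported in a previous study"; 80% power; one-sided alpha 0.025; margin 10 points; 57 per group, or 67 after 15% dropout.

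n per group = (1.960 + 0.842)² × [0.7069 × 0.2931 + 0.5546 × 0.4454] / (0.7069 − 0.5546 + 0.10)² = 56.01, rounded up to 57. Power at 57 is 80.7%. Then 57 / 0.85 = 67.06, consistent with the stated 67. The sample size reproduces and is not in question.

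**3. Illustration of the tilt**

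The documents give neither the share f of itopride-intolerant participants nor their response r on itopride, so both are assumptions. A further assumption is that these patients respond normally to acupuncture.

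- Itopride rate: p_I = (1 − f) × 0.5546 + f × r.
- Acupuncture rate, set exactly at the margin in suitable patients: p_A = 0.5546 − 0.10 = 0.4546.
- Chance of declaring non-inferiority: Φ[(p_A − p_I + 0.10) / SE − 1.96], with SE = √{[p_A(1 − p_A) + p_I(1 − p_I)] / n} and n = 67.

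Worked case, f = 5% and r = 0:

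- p_I = 0.95 × 0.5546 = 0.5269, a fall of 2.8 points.
- SE = √[(0.2479 + 0.2493) / 67] = 0.0861.
- (0.4546 − 0.5269 + 0.10) / 0.0861 = 0.322.
- Φ(0.322 − 1.960) = 5.1%, against 2.5% when f = 0.

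Range with n = 67, for no response and for half the planned response (0.5546 / 2 = 27.73%):

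| Share f | Fall in itopride rate, r = 0 | Chance, r = 0 | Fall in itopride rate, r = 27.73% | Chance, r = 27.73% |
|---|---|---|---|---|
| 0 | 0 | 2.5% | 0 | 2.5% |
| 1% | 0.6 points | 2.9% | 0.3 points | 2.7% |
| 2% | 1.1 points | 3.3% | 0.6 points | 2.9% |
| 5% | 2.8 points | 5.1% | 1.4 points | 3.6% |
| 10% | 5.5 points | 9.4% | 2.8 points | 5.1% |

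At n = 57 the worked case gives 4.8%.

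**4. Effect of dropout and imputation**

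The r = 0 column counts every intolerant patient as an observed non-responder. If they stop and their outcomes are missing, imputation under missing at random draws on the patients who remain. The estimated itopride rate then moves back towards 55.46%, and the chance towards 2.5%. The r = 0 column is therefore an upper end for each share.

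**The case against.** The best case for the plan has four parts.

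- **Needling is common to all arms; itopride is not.** Every participant has 12 verum or sham sessions, and sham needling also pricks, so tolerating it is a condition of taking part at all. Only one arm in three receives active itopride. This explains why acupuncture tolerance is listed. It does not explain leaving itopride out, since nobody knows at screening who will be allocated to it.
- **The article condenses a fuller protocol.** Drug hypersensitivity may be handled there, in the product label or by the screening clinician, and section 2.2 requires experienced practitioners. That may well limit the problem in practice. But the article prints eligibility as an explicit numbered list that names tolerance for one active treatment only.
- **Numbers are probably small.** The Discussion describes itopride as having higher drug safety, and nothing suggests that known intolerants are common. This stands, and it is why no headline magnitude is claimed.
- **Randomisation protects the comparison.** Within the enrolled population the comparison is unbiased and its error rate nominal. This also stands. The figures above describe a shift away from the population suited to both treatments, not an error in the randomised comparison itself.

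A reader might go further and infer that the criteria also favour acupuncture by admitting earlier itopride failures. The documents do not support that. Earlier acupuncture failures are not named either; both treatments have the same two-week rule; and the undefined non-refractory criterion may already remove some patients who failed drug treatment. If earlier itopride failures also respond equally less to acupuncture, there is no tilt at all. Excluding itopride failures alone would create a new asymmetry.

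**Conclusion.** The point holds for tolerance only. Section 2.3.2 excludes known intolerance of acupuncture and is silent on known intolerance of, or hypersensitivity to, itopride, although any participant may be allocated to it. The safety concern follows directly from the text. The effect on the non-inferiority comparison has a clear direction, towards acupuncture, but no size that the documents can supply.

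The doubling from 2.5% to about 5% rests on an assumed 5% share, no response on itopride in those patients, normal response to acupuncture, their outcomes being observed, and a target population of patients suited to both treatments. It shows only that a small share could matter against a 10-point margin. It is not an estimate for this trial. No conclusion is drawn about patients in whom itopride previously failed to work.

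**What to change.** Reword exclusion (2) so that it covers known intolerance of, or hypersensitivity to, either study treatment, acupuncture or itopride. If the full protocol already says this, bring the published list into line with it. Section 2.10 requires ethics committee approval for any protocol change, and recruitment is scheduled to run until December 2027, so an amendment can still take effect. The cost is one amended line, one question at screening, and a few patients lost to recruitment. The sample size does not change.
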